## 2. Amendments and updates

**Table 1 – Study protocol amendments and updates regarding previous approves by CEFCM-UNL**

| Number | Date
(dd/mm/YYYY) | Section of study
protocol                 | Amendment or
update                                                                   | Reason                                                                                                                                                                                                                                                                                                                                                                                                                        |
|--------|----------------------|----------------------------------------------|------------------------------------------------------------------------------------------|-------------------------------------------------------------------------------------------------------------------------------------------------------------------------------------------------------------------------------------------------------------------------------------------------------------------------------------------------------------------------------------------------------------------------------|
| 1      | 01/07/2022           | 6.6 Participant
timeline                  | Start and End of
study data
collection                                             | Because of COVID-19 we had to extend the beginning of the start of the study data collection. Additionally, there was a need to change the study geographic region from the Centre to the North region of Portugal which delayed the beginning of the study.                                                                                                                                                                  |
| 2      | 01/07/2022           | 5. Study design
6.1. Study setting        | The geographic
region, FHUs and
pharmacies where
the study will be
conducted | Because the first region considered (Aveiro) to conduct the study, had a similar intervention running in the primary care units, we needed to change the intervention region. Currently, we aim to conduct the study in Alto Minho (ACES Alto Minho) region. New intervention and control FHUs and pharmacies were identified and included. The details of the intervention region and control FHUs were updated accordingly. |
| 3      | 01/07/2022           | 6.2. Pharmacy
invitation /
recruitment | Pharmacies                                                                               | Because eligible study pharmacies are those within the geographical area of the identified FHUs, new pharmacies had to be identified.                                                                                                                                                                                                                                                                                         |
| 4      | 01/07/2022           | 6.3.1 Patients'
inclusion criteria        | Intervention and
control FHU listed
as an inclusion
criterion                   | The characteristics of the new intervention and control FHUs were updated according to the geographical change                                                                                                                                                                                                                                                                                                                |
| 5      | 01/07/2022           | 9.1. Research
ethics approval             | Inclusion of a new
Ethics Committee
assessment (CES-
ULSAM)                     | Because the study will be conducted in Alto Minho, an ethical assessment of the CES-ULSAM is required                                                                                                                                                                                                                                                                                                                         |

Milestones

**Table 2 - Planned dates of study milestones**

| Milestone                             | Planned date                                                                                                             |
|----------------------------------------------|---------------------------------------------------------------------------------------------------------------------------------|
| Study Protocol and Privacy Impact Assessment | December 2020                                                                                                                   |
| Ethics Clearance                             | February 2021(CEFM-UNL)                                                                                                         |
| Pharmacist and physicians training           | September / October 2022 ( $\pm 4$ months considering Ethics approval)                                                          |
| Start of data collection                     | October 2022 ( $\pm 4$ months considering Ethics approval)                                                                      |
| End of data collection                       | When full sample size estimate is reached with additional 6-month follow-up per patient (Estimation: March 2023 $\pm 4$ months) |
| Final report of study results                | To be defined                                                                                                                   |
| Manuscript submission                        | To be defined                                                                                                                   |

### **3. Background and Rationale**

Population ageing is one of the greatest social and economic challenges across European Union (EU). The number of elderly people in the EU-28 rose, over the last two decades, at a rate that was almost six times as fast as for the overall population (1). In Portugal, currently, elderly account for more than one fifth of the total population, one of the highest shares in the EU. It is expected to exceed one-third by 2050 (1). Despite a positive increase in life expectancy, many face multiple health conditions or mobility problems in their last years (2). A recent study found that multimorbidity (presence of two or more chronic conditions) was present in 92.6% (CI:90.7-94.6) of people with 65 or more years attending primary care in Portugal (3).

Studies show that medicine consumption has increased in recent years (4,5), with older people being the largest per capita consumers (6). According to national data, the National Health Service (NHS) per capita medicines consumption was 15.8 in 2015 and increased to 16.5 in 2018 (7). Almost half of the medicines are used by people with more than 80 years old (8), with prescription medicine expenditures becoming particularly high for older adults (9). For example, in the USA, the average annual expenditures for people aged 80 and older are almost 1.5 times higher than those for people aged 50 to 64 years (\$560 vs \$796, respectively)(10).

Polypharmacy is widespread and increasingly common, driven by this growth of ageing population, increasing prevalence of multimorbidity and evolution in the complexity of therapeutics (11–14). As people get older there are also physiological changes, which impact the pharmacodynamics and pharmacokinetics of medicines, changing the benefit/risk ratio of medications. Approximately 1 in 5 medicines commonly used in older people may be inappropriate (15). Medications may be appropriate when initiated for an indication, but insufficient monitoring and follow-up, or even transfer between providers and care settings, can contribute for continued use to be inappropriate, with an outcome ranging from none (or poor) therapeutic benefit to severe harm and possible death(16). Globally, in 2017 the World Health Organization (WHO) refers that the cost associated with medication errors has been estimated at US\$ 42 billion annually (17).

Potentially inappropriate medication (PIM) is defined as a medication in which the risk of an adverse event outweighs its clinical benefit, particularly when there is a safer or more effective alternative therapy for the same condition, so that its use should be avoided (18).

PIM has been identified as one of the main risk factors for adverse drug events (ADEs) in the elderly (19–22). PIMs can lead to a loss in quality of life, greater health care service use and, consequently higher health care cost among older adults (23–25). A study conducted in Canada found that patients presented to the Emergency Department (ED) with ADEs experienced a higher risk of additional in-patient days (6.3% versus 3.4%; odds ratio 1.52; 95% CI 1.43 to 1.62) and a higher rate of outpatient health care encounters (1.73 versus 1.22; rate ratio 1.20; 95% CI 1.03 to 1.40), compared with patients presenting for other reasons. The adjusted median monthly cost of care was 1.90 times higher (Can \$325 versus \$96; 95% CI 1.18 to 3.08) (26). In Europe, 8.6 million unplanned hospitalisations occur every year due to ADRs (27), with twice as many patients aged 65 years and older being hospitalized than their younger counterparts (28). However, ADEs can be difficult to recognize in older people and be attributed to a specific medicine, as they often take several medicines and present nonspecific symptoms, which may have several etiologies like fatigue, falls, or osteoporosis (29). Preventing harm due to medicines is a global patient safety challenge (17) that can improve health and reduce demands for the healthcare system reducing threats to service sustainability. However, General practitioners (GPs) face major challenges to balance benefits and risks. Besides lack of time to manage polypharmacy (30), they also need to coordinate prescribing from multiple specialists.

Patient safety is one of the most important components of health care delivery. Deprescribing has been proposed as a method of reducing polypharmacy and improving medication use throughout a patient's path of care. It is a structured process of reduction or discontinuation of inappropriate medication that might be causing harm or might no longer be providing benefit, supervised by a health care professional (31–33). Evidence supporting the benefits and safety of deprescribing has growing in recent years (34,35). A recent review (36) concluded that successful deprescribing interventions are facilitated by the combination of behavior change techniques (BCTs) involving a range of intervention components such as defining a goal and an action plan to solve inappropriate prescription, clear instructions and guidance, information about potential risk and consequences of deprescribe or not deprescribe. Various studies also identified the necessity and benefits of multidisciplinary collaboration when addressing polypharmacy (37). Ideally the withdrawal plan should be developed in a cooperative process between the patient, the physician and the community pharmacist, followed by a close monitoring during, and after medication withdrawal (33,38–40).

Uncertainty and avoidance of harm as adverse drug withdrawal events return of medical condition(s), reversal of drug-drug interactions and damage to the health professional-patient relationship, has

been commonly reported as a barrier to deprescribing. However, research has shown that community dwelling elderly are willing to undertake deprescribing, especially if they take a large number of medications, are experiencing side effects or feel some medications are no longer necessary (41–44). Moreover, evidence suggests that patients with multimorbidity incur high levels of out-of-pocket expenditures (OOPE) on medicines and that the elderly and low-income groups were most vulnerable to higher OOPE (45). In Portugal, this issue is very relevant specially when there are problems of access to health care (46,47). The reduction or withdrawal of unnecessary medicines, by reducing OOPE, can also encourage patients to follow the health professional indication. The need to receive health professional support and follow-up by various means, if a medication was discontinued, and the insurance that the medication could be restarted, if necessary, a major factor of success (42,43,48). Many studies reported a high prevalence of PIM in European community-dwelling older adults (20). National research has also showed a high prevalence use of inappropriate medicines among elderly across Portugal (49–51). Simões *et al* found that PIM was present in 68.6% (95% CI 65% to 72%) of older adult population within primary care in Portugal (51). These results suggest there is an opportunity to act and deprescribe. Medicines inappropriately prescribed or used for too long, can contribute to polypharmacy with its attendant risks of nonadherence, prescribing cascades drug interactions, medication errors, emergency department visits, and hospitalizations (52).

Proton pump inhibitors (PPI) are a class of medications that reduce gastric acid secretion and are used for treating many conditions such as gastroesophageal reflux disease (GERD), dyspepsia, reflux esophagitis, peptic ulcer disease (PUD), and as part of the eradication therapy for *Helicobacter pylori* (*H. pylori*) infection (53). They are also used to prevent and reduce the risk of ulcers in people with a history of PUD and in people who use chronic nonsteroidal anti-inflammatory drugs (NSAIDs) (54). Although short-term use of PPI appears relatively safe, long-term use as been associated with *Clostridium difficile* infection, hip fracture, chronic kidney disease (CKD) diarrhea, impaired B12 absorption, hypomagnesaemia, or community-acquired pneumonia (55–59). Yet, studies consistently show that PPI are being overprescribed worldwide (60–62). Evidence suggests that adverse effects from long-term use of PPI are increasing, and that older people are more susceptible to them (63). Treatment should be given at the lowest effective dose that controls symptoms, and for the minimum period (64). It is estimated that between 25% to 80% of people are prescribed a PPI inappropriately (31,65–67), being frequently reported as one of the most prescribed class of PIM among the elderly. This inappropriate use incurs a financial burden to the patient and high costs to the health system. In

2016, the PPI' costed to the Portuguese NHS €19.9 million and €37.9 million to patients (68). Pantoprazole, a common PPI, was among the top 10 most consumed medicines in ambulatory care in Portugal in 2019. Pantoprazole market sales increased by 5.8% compared to 2018 (69). Therefore, it is prudent to discontinue unnecessary PPI.

PPI are frequently addressed in diverse available screening tools used to identify PIMs in older adults (70–73) Beers Criteria, one of the most known and used criterion in the world (74), strongly recommend, with high-quality evidence, to avoid scheduled use of PPI for >8 weeks except for high-risk patients (eg, oral corticosteroids or chronic NSAID use), erosive esophagitis, Barrett esophagitis, pathological hypersecretory condition, or demonstrated need for maintenance treatment (eg, because of failure of drug discontinuation trial or H2-receptor antagonists) (71). Despite the existence of these tools and national guidelines to help health care professional to improve prescription, inappropriate use of these medicines persists. PPI were one of the most frequently class of PIMs found in Simões *et al* observational nationwide study (51). Furthermore, this class of medicines in the lower doses is classified as over the counter (OTC) drug, which makes their access easier for patients.

Successful deprescribing may result in reduced medication burden, ADEs and costs (34), although it is unclear if withdrawal of medicines may significantly improve patients' quality of life (QoL) or mortality (35,75).

Due to limited resources, patients who may benefit from deprescribing need to be prioritized. Qualitative research has shown that not only patients are receptive to make changes to their PPI (76) but also health professionals pointed this class of medications as a priority to deprescribe supported by evidence-based guidelines (77). Communication and deprescribing efforts shared between physicians, pharmacists, and patients, may enhance the inappropriate medication withdrawal process keeping it safe and maintaining the patient trust (78). Multidisciplinary collaborations to deprescribe in primary care seem to be successful to optimize prescription and medication use in different settings and models(79–81). Despite these interventions and collaborations are potentially costly and time consuming, few studies addressing the cost-effectiveness of trials to reduce PIM have been conducted (82–84)

In Portugal healthcare is mostly provided in a very fragmented way, both between primary and hospital care within the NHS and, between the NHS and the private sector like the community pharmacy one. Indeed, these sectors are organized and financed in different and independent ways, and the

incentives for collaboration are mostly absent. Using this knowledge and for the purpose of this study we will consider a collaborative model, as the establishment of formal links between community pharmacies and primary care units, with the aim of improving medicines use among elderly in Portugal.

The C-SENioR (Collaborative Deprescribing Intervention of PPI on community dwelling elderly) trial aims to determine whether a general practitioner and community pharmacist collaborative deprescribing intervention targeting community-dwelling elderly- is effective and cost-effective compared to usual care.

#### **4. Aim and objectives**

The aim of this study is to evaluate the effectiveness and the cost-effectiveness of a community pharmacist-general practitioner collaborative deprescribing intervention of proton-pump inhibitors among the community dwelling elderly.

##### **Primary objective**

To evaluate the effectiveness of a community pharmacist-general practitioner collaborative intervention on the discontinuation of inappropriate PPI by community dwelling elderly, compared with usual care, as measured by the cessation or reduction of targeted medication at 6 months follow-up. The acronym C-SENioR stands for “Collaborative depreScribing intervENTION of PPI on community dwelling eldeRly”.

##### **Secondary objectives**

To assess the intervention impact on medication burden (total medicines) and on prescription optimization (drug-drug interactions); to assess time to PPI discontinuation; to understand if the intervention affects participants’ beliefs with respect to inappropriate medicines and self-reported medication adherence; to evaluate the intervention implementation through process indicators, and to assess patient’s satisfaction with the collaborative intervention.

##### **Exploratory objectives**

To explore factors (sociodemographic characteristics, clinical history, beliefs, others) potentially associated to patient’s medication discontinuation.

## 5. Study Design

This is a pragmatic, multicentre, non-randomised controlled trial with a follow-up period of 6 months of a collaborative Pharmacy-Family Health Unit deprescribing intervention. There are two-arms in this controlled trial: the intervention arm (collaborative intervention) and the control arm (usual care). Pragmatic trials are undertaken in the real world under the context of a real-life setting and the results are intended to support a decision to deliver the intervention in a routine practice (85).

An experimental design with random assignment was not feasible since the collaborative intervention was developed based on the expressed interest of two specific family health units (FHUs) – FHU Terra da Nóbrega in Ponte da Barca municipality and FHU Uarcos municipality in Arcos de Valdevez (both belonging to Aces Alto Minho, Unidade Local de Saúde do Alto Minho). Randomization at patient level was not considered to prevent individual contamination, due to controls and interventions being exposed to the same environment (pharmacies and FHUs). Each FHU unit and surrounding pharmacies will consist of a study site (intervention or control).

The Ponte da Barca and Arcos de Valdevez sites will comprise the intervention arm. Control sites will be selected from other geographical regions with characteristics like the intervention study sites.

Patients will be recruited through community pharmacies. A 1:1 ratio (intervention:control) of participants will be used. The flowchart of the C-SENIoR trial is illustrated in Figure 1.

An Economic evaluation will be conducted alongside the trial, meaning the collection of costs and outcome data alongside the trial.

[figure not shown]

Figure 1 - Study Flowchart

## **6. Methods**

### **PARTICIPANTS, INTERVENTIONS, AND OUTCOMES**

#### **6.1. Study setting**

This study will be carried out in the primary care setting involving community pharmacies and Family health Units (FHU) in Portugal mainland.

FHUs' collaboration for the intervention arm development was established with two FHUs from the Health Centres Group - ACES Alto Minho/ULSAM in Viana do Castelo district, which showed interest to participate in a community pharmacist-general practitioner collaborative trial in primary care. The ACES Alto Minho (AM) comprises a geographic region of ten municipalities in the north region of Portugal with about 232 178 inhabitants in 2017: Arcos de Valdevez, Caminha, Melgaço, Monção, Paredes de Coura, Ponte da Barca, Ponte de Lima, Valença, Viana do Castelo, Vila Nova de Cerveira. Viana do Castelo is one of the most aged districts in Portugal. In 2018, the ACES AM Ageing Index was 220,3% and the old age dependency rate 39.2%, well above the mainland average (162.2% and 22.9 respectively). Moreover, the illiteracy rate (6.8%) was above the mainland average. For the 2016-18 triennium, the life expectancy at birth was 80.81 years, which is very similar to the national value (80.99) (86).

Form the intervention arm, pharmacies who fulfilled the following criteria will be invited to participate ( $\approx$ 9 pharmacies):

- Be affiliated in ANF (which represent 95% of the Portuguese community pharmacies).
- Location in the same municipality of the identified FHUs.
- With Sifarma® dispensing software ( $\approx$ 84% of all community pharmacies), to allow researchers to extract electronic data, on the acquisition of medicines by patients.
- With registered prescription sales from identified FHU

It is expected that the proportion of pharmacies accepting to participate in the intervention arm will be high (about 80% of the total invited) since this is an innovative health care service, involving multidisciplinary teams and collaborative interventions delivered by professionals from FHUs and Pharmacies. The recruitment strategy will be reinforced by several initiatives (e.g., telephone contacts

made by the principal investigator to the technical director of the invited pharmacies) to engage the participation of pharmacies.

To avoid contamination bias, different geographic regions were chosen for the recruitment of control pharmacies and patients. The control selection involved the identification of the best-matching to intervention setting characteristics, firstly in terms of municipality sociodemographic characteristics and secondly in terms of existence of FHUs with similar traits of the intervention FHU (type and PPI consumption).

The following criteria was used to identify control regions for intervention study sites:

- 1) Municipalities with most similar characteristics of intervention sites (Arcos de Valdevez e Ponte da Barca), as estimated by three-dimensional normalized Euclidean distance, considering:
  - Municipalities *per capita* Purchasing Power (PP) ('Índice de Poder de Compra Concelhio per capita', 2019) (INE, 2022)
  - Municipality Aging ratio (AR) ('Índice de Envelhecimento no Concelho', 2020) (INE, 2022)
  - Municipality Illiteracy Rate (IR) ('Taxa de analfabetismo (%) por Local de residência', 2011) (Pordata, 2020)
- 2) FHUs from identified municipalities considering:
  - Contractual NHS type - Type "A" or "B" as the intervention units, as governance and funding models differ from FHU type (A or B).
  - Prescription volume of PPI per 1000 elderly ( $\geq 65$  y) in 2021, as FHU age pyramid (2022, data extracted in June 2022 from the site BI-CSP) most similar with the FHUs intervention. It was accepted a maximum absolute variation of 20% in comparison with the estimated value of the FHU intervention.

Additionally, it is planned to enroll more municipalities in the control arm to guarantee a similar number of participating pharmacies, as a lower pharmacy recruitment rate is expected in this group compared to the intervention. We expect an average pharmacy participating rate of about 20% (about  $\frac{1}{5}$  of the expected rate of the Intervention group) as previous found in others non-interventional studies conducted in pharmacies (source: CEFAR).

After identification of the FHUs, control pharmacies will be identified based on the same criteria used for intervention pharmacies. All the identified pharmacies will be invited to participate (≈60). Detailed information of the intervention and control municipalities and FHUs are depicted in Table 3.

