**Table 3 - Details of the intervention and identified municipalities and control FHUs**

| Group        | FHU name and Type          | N.elderly
Registered at
FHU | N. GP (BI-
CSP, 2022) | Municipality / District              |
|--------------|----------------------------|-----------------------------------|--------------------------|--------------------------------------|
| Intervention | Uarcos - B                 | 3546                              | 7                        | Arcos de Valdevez / Viana do Castelo |
|              | Terra da Nóbrega - A       | 3573                              | 10                       | Ponte da Barca / Viana do Castelo    |
|              | Senhora da Graça – B       | 1911                              | 11                       | Mondim de Basto / Vila Real          |
|              | Penela -B                  | 1910                              | 4                        | Penela / Coimbra                     |
|              | Baião – B                  | 1812                              | 6                        | Baião / Porto                        |
|              | Lethes – B                 | 3436                              | 9                        | Ponte de Lima / Viana do Castelo     |
|              | Mais Saúde - B             | 2071                              | 5                        |                                      |
|              | D’As Terras de Lanhoso – B | 2797                              | 7                        | Póvoa de Lanhoso / Braga             |
| Control      | Prado – B                  | 12339                             | 6                        | Vila Verde / Braga                   |
|              | Pró-Saúde - B              | 6976                              | 5                        |                                      |
|              | Vida+ - B                  | 12152                             | 7                        |                                      |
|              | Nova Mateus - A            | 1889                              | 8                        | Vila Real / Vila Real                |
|              | Fénix – A                  | 3266                              | 7                        |                                      |
|              | Corgo - A                  | 3111                              | 6                        |                                      |

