## 6.9. Blinding

Due to the nature of the intervention, neither patients nor pharmacist and GPs (providers) are blinded to the intervention. In addition, research team who developed this trial cannot be blinded either. However, to preserve a certain level of masking, to protect sources of bias, intervention participants will only be aware that the research team will also collect data in other geographical regions regarding usual care.

In the control group, no information regarding the intervention procedures will be provided to pharmacies and patients. The project will be presented as a medication use pattern study in the elderly. Moreover, as pharmacies allocated to each group (intervention and control) are located in distinct geographic locations, minimizing their interactions and ensuring their unawareness of each other.

FHUs in the control sites will be blind by design as they do not have any intervention in this trial, serving only to ensure that patients in both arms are subject to the same type of usual care.

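### Ponte de Lima is used as a control although the protocol places it in the same geographic region as both intervention FHUs; three elderly counts in Table 3 also need checking

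*Protocol*

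**What the plan says.** **The separation rule.** Section 5 states: "Control sites will be selected from other geographical regions with characteristics like the intervention study sites". Section 6.1 repeats the rule and gives its reason: "To avoid contamination bias, different geographic regions were chosen for the recruitment of control pharmacies and patients". The Protocol Summary says the same under Study setting. Section 6.9 builds the masking argument on it: "pharmacies allocated to each group (intervention and control) are located in distinct geographic locations, minimizing their interactions and ensuring their unawareness of each other".

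**The intervention region.** Section 5 describes the two intervention FHUs (Uarcos in Arcos de Valdevez, Terra da Nóbrega in Ponte da Barca) as "both belonging to Aces Alto Minho, Unidade Local de Saúde do Alto Minho". Section 6.1 describes that group: "The ACES Alto Minho (AM) comprises a geographic region of ten municipalities in the north region of Portugal". It then lists the ten: "Arcos de Valdevez, Caminha, Melgaço, Monção, Paredes de Coura, Ponte da Barca, Ponte de Lima, Valença, Viana do Castelo, Vila Nova de Cerveira".

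**The control list.** Table 3 has a row reading "Ponte de Lima / Viana do Castelo" for FHU Lethes, followed by Mais Saúde with an empty municipality cell, which I read as carried down. The Protocol Summary, under Study Population, names Ponte de Lima among the control municipalities. Section 6.3.1 makes the control FHUs of Table 3 an inclusion criterion.

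**The Vila Verde counts.** On the same reading of empty cells, Table 3 lists three FHUs under "Vila Verde / Braga": Prado, Pró-Saúde and Vida+, with 12339, 6976 and 12152 registered elderly for 6, 5 and 7 GPs. Section 6.1 matches FHUs on PPI prescription volume per 1000 elderly, with a maximum variation of 20%.

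**The concern.** In a non-randomised trial the choice of control sites is a main protection against bias, and here the site list departs from the rule that the protocol sets for itself. Ponte de Lima shares the district, the health-centre group and the local health unit with both intervention FHUs. Awareness of the intervention could pass between sites more easily inside one group than between distant regions. If control patients were exposed to part of the intervention, more of them would stop or reduce their PPI and the estimated difference would shrink. The statement in Section 6.9 that distance ensures the two arms do not know of each other is also weaker for these sites.

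The Vila Verde counts raise a separate and smaller question. Section 7 relies on similar PPI prescribing per 1000 elderly as a guard against confounding by GP practice. An elderly count that is wrong in Table 3 matters to that guard only if the same count was used in the matching.

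**Working it through.** **1. Is Ponte de Lima in the intervention region?**
- Section 5: both intervention FHUs belong to ACES Alto Minho.
- Section 6.1: ACES Alto Minho is one geographic region of ten municipalities, including Arcos de Valdevez, Ponte da Barca and Ponte de Lima.
- Protocol Summary and Table 3: Ponte de Lima is a control municipality in Viana do Castelo district, the district of both intervention FHUs.

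These statements cannot all stand beside the rule that controls come from other regions. The Summary names Ponte de Lima as control in running text, so this is not an effect of how Table 3 was read.

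**2. How much of the control list is concerned?** Inputs are from Table 3.
- FHUs: 2 of 17. Municipalities: 1 of 11.
- Elderly at the two FHUs: 3436 + 2071 = 5507.
- Elderly at all 17 control FHUs, as printed: 65503. Share: 5507 / 65503 = 8.4%.
- Vila Verde, as printed: 12339 + 6976 + 12152 = 31467. All other control FHUs: 65503 − 31467 = 34036.
- Assumption: true elderly per GP in Vila Verde equals the median of the other FHUs, 411. Its 6 + 5 + 7 = 18 GPs then give 18 × 411 = 7398.
- Share: 5507 / (34036 + 7398) = 5507 / 41434 = 13.3%.

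These are shares of registered elderly, not of recruited patients. Patients enter through pharmacies that volunteer, each asked for at least 10 patients (Section 6.2), so the share among recruited controls cannot be known in advance.

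**3. Elderly per GP.** Formula: registered elderly / number of GPs.
- Prado: 12339 / 6 = 2056.5
- Vida+: 12152 / 7 = 1736.0
- Pró-Saúde: 6976 / 5 = 1395.2
- Intervention FHUs: 3546 / 7 = 506.6 and 3573 / 10 = 357.3
- The 16 FHUs outside Vila Verde: 173.7 to 763.5, median 411

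Against the next-highest ratio: 1395.2 / 763.5 = 1.8; 1736.0 / 763.5 = 2.3; 2056.5 / 763.5 = 2.7. The three FHUs account for 31467 / 65503 = 48% of the listed control elderly.

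**4. What removing Ponte de Lima does to recruitment.**
- Section 6.1: about 60 control pharmacies invited, about 20% taking part: 60 × 0.20 = 12 pharmacies.
- At the minimum of 10 patients each: 120 control patients, against 111 needed per group (Section 6.11).
- Assumption: pharmacies are spread evenly over FHUs. Then 120 × 15 / 17 = about 106.

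The sample size is not in question: exact power of the two-sided Fisher test at 89 per group is 0.9017, as Section 6.11 prints.

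**The case against.** **Region may mean municipality.** Section 6.1 applies its criteria for identifying control regions to municipalities, and the Protocol Summary uses region and municipality side by side. On that usage Ponte de Lima is a different region. This shows that the term is used loosely, but it does not settle the matter, because Section 6.1 itself says that one region holds all ten municipalities.

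**No route of contamination is shown.** This stands. Section 5 names the hazard as patients sharing pharmacies and FHUs, and Ponte de Lima shares neither with the intervention sites. GP training goes only to the intervention FHUs (Section 6.5), control pharmacies are told nothing about the intervention (Section 6.9), and about 94% of PPI sales prescribed by the intervention FHUs were made at the selected pharmacies (Section 6.11). A reader might infer that controls are contaminated and that the 20-point difference will shrink by a definite amount. The protocol supports neither: it gives no rate of uptake among exposed controls and no share of recruited controls from Ponte de Lima.

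**The Vila Verde counts may be only a printing error.** This also stands. A reader might infer that they are all-age lists and that they spoiled the matching. Section 6.1 takes the age structure from the FHU age pyramid and does not say that the Table 3 figures were the denominators. At 411 elderly per GP the printed counts would be 1395.2 / 411 = 3.4 to 2056.5 / 411 = 5.0 times too high and would understate PPI volume per 1000 elderly by 71% to 80%. Such FHUs would be expected to fail the 20% limit unless their true rates were far above those of the intervention FHUs. Their presence in the table therefore fits a display error at least as well as faulty matching.

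**Conclusion.** The contradiction is real. The protocol promises controls from other regions, relies on that promise against contamination and for masking, and then lists two control FHUs inside the region of both intervention FHUs. It concerns 2 of 17 control FHUs and, by registered elderly, 8.4% as printed or about 13% with Vila Verde set to 411 per GP. The second figure rests on that assumption, and neither figure is a share of recruited patients. Contamination itself is neither shown nor sizeable from the document; its direction, if it occurred, would be toward no effect. This is a moderate design inconsistency that can be cured before invitations go out, not evidence that the trial's result would be wrong.

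The Vila Verde counts are clear outliers and should be checked. That they entered the matching is not supported by the text.

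**What to change.** **Ponte de Lima.** Preferably, remove Lethes and Mais Saúde from Table 3, and Ponte de Lima from the control municipalities in the Protocol Summary, before their pharmacies are invited. Section 6.3.1 follows, since it refers to Table 3. Fifteen FHUs in ten municipalities remain. At minimum, state and justify the exception in Section 6.1, qualify the masking statement in Section 6.9, and prespecify a sensitivity analysis of the 6-month primary outcome that leaves out control patients from these two FHUs.

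Cost: this is more than a wording change. It alters eligibility and needs an amendment, as the earlier changes of FHUs did (Table 1). The expected control pool falls from about 120 to about 106 under the even-spread assumption, against 111 needed. Ten patients per pharmacy is a minimum and Section 6.3 allows recruitment to be extended, so the shortfall can be made up.

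**Vila Verde.** Verify the three elderly counts at source and correct Table 3. If the wrong counts were the matching denominators, recompute PPI volume per 1000 elderly and recheck these FHUs against the protocol's own 20% limit. If they were not, correcting the table is enough. The cost is a data check.
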